### Data collection and management

Figure 2 provides an overview of the data collection timeline. The baseline and 1-week preoperative assessments will be conducted in the participant’s home, and the 6-week and 6-month assessments will be conducted in the orthopedic clinic. All four assessments will be conducted by blinded assessors. The study assessors received an individualized 3-day training on how to collect the study outcome measures from frail older adults. Study data will be managed using REDCap electronic data capture tools [38]. The study database will be password protected and kept on a secure network system.

### Trial management

The coordinating center for the study is at the Geriatric Education and Research in Aging Sciences (GERAS) Center, Hamilton Health Sciences. The study coordinator and research assistants will be responsible for submitting and maintaining REB documents, scheduling of home visits, receiving, and storing consent forms. The study Steering Committee will meet every 6 months to provide overall supervision of the trial. The research coordinator will call more frequent Steering Committee meetings if required. It is anticipated the final results of this study will be completed in 2018.

### Data analysis

Data from the trial will be analyzed and reported in accordance with the CONSORT criteria [33, 39]. The baseline characteristics will be reported as mean (standard deviation) or median (inter-quartile range) values for continuous variables and as counts (percent) for categorical variables. Data will be summarized in tabular or graphical form. The main between-group comparison will take place at 6 weeks post-operative. The primary feasibility outcomes will be analyzed using descriptive statistics expressed as percent and corresponding 95% confidence intervals (CI). For clinical outcome, analyses will be performed using the intention-to-treat principle. We will use linear regression for continuous variables and logistical regression for categorical variables to explore the difference between groups pre- and post-operative. Exploratory subgroup analyses will be conducted to explore the differential effect of home-based versus center-based exercise and the effect on people undergoing hip versus knee replacement. Sensitivity analysis will be conducted using the per-protocol concept (including adherent participants, who completed 70% of the intervention components (i.e., completed 70% of exercise sessions, took 70% of the vitamin D, protein supplements, and the medication review was done)) [40]. All *p* values will be reported to three decimal places with those less than 0.001 reported as *p* < 0.001. The criterion for statistical significance will be set a priori at alpha = 0.05. Analyses will be performed using STATA V13 [41].

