### Objectives

The primary objective is to examine the feasibility of a parallel group RCT comparing a preoperative multi-modal frailty intervention to usual care in pre-frail/frail older adults undergoing elective unilateral hip or knee replacement. The secondary objectives areTo explore potential efficacy of the multi-modal frailty intervention in improving frailty and mobility between baseline and 6 weeks post-surgery using Fried frailty phenotype and short performance physical battery (SPPB), respectively.To explore potential efficacy of the multi-modal frailty intervention on post-operative healthcare services use including hospital length of stay, rate of complication after hip or knee replacement, readmission to the hospital, and number of emergency room (ER) visits.

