### Randomization and consent

Once the study research assistant confirms the patient’s eligibility, and obtains informed written consent, the research assistant will submit the eligibility form, consent form, and participant contact form to a team member (who is not part of the study) who will randomize the participant to the intervention or usual care group based on stratified block randomization list. To ensure an equal number of participants in the study groups, the allocation ratio will be 1:1. Participants will be stratified based on their age (≥ 80 or ≤ 79 years) and approximate waiting time (≥ 6 or < 6 months). The allocation sequence will be computer generated using SAS 9.3 software [25]. To conceal the sequence, only a researcher who is not involved in the study will have the computer-generated allocation list.

After randomization, a blinded outcome assessor will contact the participants to set up an appointment for the baseline assessment. After the baseline assessment, the study research coordinator will inform the participants of their study group. The intervention group participants will be contacted by the study intervention kinesiologist to arrange the first intervention visit.

Those blinded to the intervention will include the outcome assessors who conduct assessments at the RJAP and in participant homes, the clinic administration, data entry personnel, data analysts who performs the final data analysis, the investigative team, and members of the steering committee. The patient will also be blinded at the baseline assessment. The study coordinator, study intervention kinesiologist, and participants will not be blinded.

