#### Secondary outcomes

Frailty will be assessed using (1) Fried frailty phenotype which is composed of five items, three self-reported (unintentional weight loss, exhaustion and physical activity), and two performance-based items (strength (assessment based on the handgrip strength measurement) and gait speed). It is a widely used and validated frailty measure [11, 34]. Each item is scored 0 or 1 with a final score out of 5; higher scores indicate greater frailty; and (2) short performance physical battery (SPPB) (made up of three assessments [35]: (a) the 4-m walk test (walking speed); (b) chair rise: balance and coordination (the ability to rise from a chair without arms); and (c) the standing balance test). The participant is evaluated on each assessment using a score between 0 and 4. A final summary performance score out of 12 is calculated, with higher scores indicating superior lower extremity function [35]. The SPPB has also been validated and has demonstrated good internal consistency and responsiveness [36, 37]. Healthcare service use (including patients’ medications/supplements (dose, frequency, and duration), discharge destination, length of hospital stay, rehospitalization rate, number of visits to general practitioner, emergency room, specialists, and physiotherapist, and number of home exercise sessions) will be collected using a form specifically developed for this study. Other outcomes listed in Fig. 2 will be collected. The study outcomes will be collected at the baseline, 1 week pre-operative, and 6 weeks and 6 months post-operative.

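### The 6-week comparison of Fried score and SPPB is stated without the baseline value; adjusting for it would sharpen the estimate from data already collected

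*Protocol article*

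**What the plan says.** All references are to the protocol article.

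- **Data analysis** gives the method for clinical outcomes: "We will use linear regression for continuous variables and logistical regression for categorical variables to explore the difference between groups pre- and post-operative". It fixes the time point: "The main between-group comparison will take place at 6 weeks post-operative". It goes on to name subgroup analyses, a per-protocol sensitivity analysis, the alpha level and the software. It mentions no baseline value, stratification factor or other covariate, and it does not say that the models are unadjusted.
- **Objectives** sets the exploratory efficacy question for Fried phenotype and SPPB as an effect "in improving frailty and mobility between baseline and 6 weeks post-surgery".
- **Secondary outcomes** gives the visits: "The study outcomes will be collected at the baseline, 1 week pre-operative, and 6 weeks and 6 months post-operative".
- **Randomization and consent** allocates "based on stratified block randomization list", and "the allocation ratio will be 1:1". The strata are age (80 and over, or 79 and under) and approximate waiting time (6 months or more, or less).

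**The concern.** The objective is about improvement from baseline, but the analysis is described as a group difference at 6 weeks. The text is compatible with three analyses of a continuous outcome: the 6-week value alone, the change from baseline, or the 6-week value adjusted for baseline. Under randomisation all three estimate the same mean difference, but with different variances. The most literal reading, the 6-week value alone, makes no use of a measurement the trial has already taken.

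Two things are at stake. First, randomisation is stratified on age and waiting time, not on frailty or SPPB, so balance on those two measures is left to chance with about 31 per arm. Second, the section on theory and development framework lists estimating the treatment effect and its variance among the pilot's scientific aims. The variance carried into the definitive trial depends on which model produced it. A 6-week-only variance would oversize a definitive trial that adjusts for baseline.

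**Working it through.** **Inputs from the protocol.** N = 62 (Sample size), 1:1 allocation, so 31 per arm. Outcomes are measured at baseline and 6 weeks.

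**Inputs assumed.** The baseline-to-6-week correlation r is not given; 0.3, 0.5 and 0.7 are shown. The low end belongs in the range because surgery and a wait of several months fall between the two measurements. The standard deviation (SD) is taken as equal at both times, and the Fried score (0 to 5) is treated as continuous.

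**1. The plan's own figure.** For a 95% interval of ±10 points around 80%, n = 0.8 × 0.2 × (1.96/0.10)² = 61.46, rounded up to 62. It reproduces. It rests on a feasibility proportion, so nothing below affects it.

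**2. Variance of the group difference relative to the 6-week value alone (1.00).** A change score has factor 2(1 − r); the baseline-adjusted value has factor 1 − r². The confidence interval (CI) width scales with the square root.

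| r | Change score | Adjusted | Adjusted CI vs 6-week only | Adjusted CI vs change score |
|---|---|---|---|---|
| 0.3 | 1.40 | 0.91 | √0.91 = 0.954: 5% narrower | √(0.91/1.40) = 0.806: 19% narrower |
| 0.5 | 1.00 | 0.75 | √0.75 = 0.866: 13% narrower | √(0.75/1.00) = 0.866: 13% narrower |
| 0.7 | 0.60 | 0.51 | √0.51 = 0.714: 29% narrower | √(0.51/0.60) = 0.922: 8% narrower |

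**3. In outcome units.** With 31 per arm the 6-week-only half-width is 1.96 × √(2/31) = 0.498 SD. Adjusted, it is 0.475, 0.431 or 0.356 SD for r = 0.3, 0.5 or 0.7. The same precision without adjustment would need 62/0.91 = 68, 62/0.75 = 83 or 62/0.51 = 122 participants. With 50 analysed (25 per arm, for illustration), 0.554 SD becomes 0.529, 0.480 or 0.396 SD.

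**4. What the strata add.** Simulation of 4,000 trials of 62 for each r, in blocks of 4. Assumptions: 20% aged 80 or over, 50% waiting 6 months or more, strata explaining 10% of baseline variance. Mean standard errors (SE) for r = 0.3, 0.5, 0.7:

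- Group only: 0.2525, 0.2527, 0.2531.
- Group and strata: 0.2518, 0.2498, 0.2469, which is 0.3%, 1.1% and 2.4% smaller.
- Group and baseline: 0.2432, 0.2206, 0.1822.
- Group, baseline and strata: 0.2438, 0.2211, 0.1825, which is 0.2 to 0.3% larger than with baseline alone.

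The last model is still about 3%, 13% and 28% below group only, close to the formula. Type I error of the group-only test was 4.7%, 4.7% and 4.6%, against a nominal 5%. Under these assumptions nearly all the gain comes from the baseline value.

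**The case against.** The strongest objection is that the protocol names a family of models and is silent on covariates. Linear regression covers a baseline-adjusted model as well as an unadjusted one, and the stated objective itself points towards using the baseline value. A journal article may leave a covariate list to the full protocol or analysis plan. This stands as far as it goes. A reader might infer that the plan commits to unadjusted, single-visit models; the documents do not say so, and the loss computed above is conditional on that reading.

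Three further limits also stand.

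- The gain depends on a correlation the documents do not give. It is small at 0.3, and against a change score it shrinks at high correlation.
- The figures hold for continuous outcomes with a baseline value. Length of stay, complications and readmission have none. In logistic regression, covariates change the target to a conditional odds ratio and do not shrink its standard error.
- Baseline is collected, so the correlation and residual variance can be recovered later whichever model is reported.

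What the objection does not remove is that the analysis as described stops short of the objective it serves, while the better-matched model costs no data.

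**Conclusion.** The point holds as a free improvement, not as an error. Run as written on the 6-week value, the comparison of Fried score and SPPB is valid. Baseline adjustment would narrow its confidence interval by about 5%, 13% or 29% at an assumed correlation of 0.3, 0.5 or 0.7, with equal variances at the two times.

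Two stronger conclusions are tempting and are not supported. One is that leaving out the strata makes the standard errors materially too large: in the simulation the effect was at most about 2%, and nothing once baseline was included. The other is that a 6-week regression would discard 20% of participants: the 80% in the Sample size section is a feasibility criterion, not a forecast of missed 6-week visits.

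The consequence is confined to exploratory comparisons and to the variance passed to the definitive trial. The primary feasibility analysis and the 62 are unaffected.

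**What to change.** Add to the Data analysis section, before any unblinded analysis, wording such as: *Fried score and SPPB at 6 weeks after surgery will be compared between arms by linear regression adjusted for the baseline value of the outcome, age stratum (≥ 80 or ≤ 79 years) and waiting-time stratum (≥ 6 or < 6 months), as recorded at randomisation. The residual variance and the baseline-to-6-week correlation will be reported for planning the definitive trial.*

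The strata are included so that the model matches the randomisation; negligible extra precision should be expected from them. A repeated-measures model over the three post-baseline visits is optional. It would keep participants who miss only the 6-week visit, but it recovers nothing for anyone with no follow-up. The covariate set should not be carried over to sparse binary outcomes, where 62 or fewer participants and a possibly thin stratum aged 80 and over could make the fit unstable. No precision gain should be claimed for outcomes with no baseline value.

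The cost is two sentences, with no new data and no change to the sample size.

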### Kinesiologist visit schedule and delivery of coaching/supplements

After randomization, the study intervention kinesiologist will phone the participant to book a home visit where goal setting will be done. During months 2–10, the study intervention kinesiologist will have bi-weekly contact (one monthly visit and one phone-call in the interim) [28] to check on progress. At the visits, the kinesiologist will adjust programs as needed, provide ongoing coaching/education, and deliver vitamin D/protein supplements. We will use exercise-reporting guidelines (CERT) to guide reporting the exercise component of the intervention [29]. Participants will be encouraged to use the Borg Rating of Perceived Exertion 10-point Scale to monitor their perceived effort levels and exhaustion for each exercise component (1 means rest/no effort and10 means maximal effort) [30]. Participants will be asked to work in a 5–7/10 workload (i.e., 50–60% of their maximal heart rate). The Borg Scale will help participants to work based on how they are feeling, which is safer for the geriatric population. In the first intervention visit, the study kinesiologist will ask the participants if they would prefer to do center-based or home-based exercise, or both.

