### Control group

Patients in the control group will receive usual care, which may include recommendations from their orthopedic surgeon to attend exercise programs, fitness and educational classes, physiotherapy referral, pool therapy, or weight loss program before surgery. However, these patients will not receive any support from the study intervention kinesiologist. Participants in the control and intervention groups will be instructed to complete a dietary intake log (including days of the week and weekend days) that indicates the type of food and amount ingested over a 4-day period in order to calculate energy and micronutrient consumption.

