Medical Research Council criteria define a “complex intervention” as interventions that are built up from a number of components, which may act both independently and inter-dependently [44]. These components include behaviors, behavior parameters, and methods of organizing those behaviors, and they may have an effect at the individual patient level, organizational, or service level or population level (or all of these in some cases). As any complex intervention, the Fit Joints intervention has several articulating components (including center and/or home-based tailored exercise program, cognitive behavioral coaching, protein and vitamin D supplements, and medication review). It is a challenge to (1) standardize all these intervention components and (2) determine the contribution of each intervention component and any interaction between these components [25]. Phase 0 (choosing an intervention theoretical model) and phase 1(identify the intervention components and the supporting evidence) of the Medical Research Council framework have been completed. The proposed study represents phase 2 of the Medical Research Council framework (which is examining the feasibility of the intervention). After completing this pilot study, we will complete phase 3 (definitive study) and phase 4 (dissemination and implementation).

The proposed study has some limitations. Participant recruitment will take place within one hospital site, which may limit its generalizability to other hospital care settings. Fit Joints investigators have considered the challenge of applicability to other settings during the study protocol development. Participants will be offered to do center-based or home exercise; however, some participants may not have access to the center-based exercise due to various reasons such as lack of time or transportation. Also, the pre-operative assessments will occur in different time points for different participants due to the variable intervention duration and that might lead to heterogeneity of the intervention effect across participants.

Strengths of our proposed study include (1) valid and reliable patient reported measures were used; and (2) Fit Joints study engaged all key stakeholders in the process of implementation, including patients, interdisciplinary healthcare teams, community organizations, and researchers. Having each perspective will enhance the participants experience throughout the study course.

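### Home versus center exercise is chosen after randomisation and only in the intervention arm, so the planned subgroup analysis cannot give a randomised treatment effect by setting

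*Protocol article*

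**What the plan says.** The Data analysis section plans two exploratory subgroup analyses in one sentence. One is by joint (hip or knee). The other is by exercise setting: "Exploratory subgroup analyses will be conducted to explore the differential effect of home-based versus center-based exercise".

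Four other places in the protocol article determine what the setting variable is:

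- **How it is set** (Kinesiologist visit schedule and delivery of coaching/supplements). At the first intervention visit, "the study kinesiologist will ask the participants if they would prefer to do center-based or home-based exercise, or both". It is the participant's choice, and there are three options.
- **When it is set** (Randomization and consent). Randomisation comes first, then the baseline assessment. Then "After the baseline assessment, the study research coordinator will inform the participants of their study group". Only after that: "The intervention group participants will be contacted by the study intervention kinesiologist to arrange the first intervention visit".
- **In whom it is set** (Control group). Of the controls the article says that "these patients will not receive any support from the study intervention kinesiologist".
- **What may drive it** (Discussion, limitations). The authors note that "some participants may not have access to the center-based exercise due to various reasons such as lack of time or transportation".

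Setting is not a randomisation factor: "Participants will be stratified based on their age (≥ 80 or ≤ 79 years) and approximate waiting time". The article mentions no recording of preferred setting in both arms.

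**The concern.** A differential treatment effect is a difference between treatment effects. It needs an intervention-versus-control comparison within each level of the subgroup variable, and a variable that allocation cannot have influenced. Joint meets both conditions, because it is known at eligibility in every participant. Exercise setting meets neither. Placing the two in the same sentence invites readers to give them the same standing.

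At stake is how one exploratory result is read. A difference between home and center users could reflect who chose each setting and be reported as an effect of the setting.

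**Working it through.** **1. Can the subgroup effect be formed?** The order of events is: randomisation, baseline assessment, disclosure of the arm, first intervention visit (intervention arm only), choice of setting. This gives the following layout:

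| | Home | Center | Both | Not defined |
|---|---|---|---|---|
| Intervention | yes | yes | yes | – |
| Control | none | none | none | all |

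The effect in the home group would be the intervention mean minus the control mean among home participants. The second term does not exist, and the same holds for center. An arm-by-setting interaction therefore cannot be fitted. Usual care does not fill the gap. The article says "Patients in the control group will receive usual care, which may include recommendations from their orthopedic surgeon to attend exercise programs", but that is a possible recommendation, not the trial's choice between settings.

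Two contrasts can be computed: home versus center within the intervention arm, and each setting against all controls. In both, at least one side is self-selected, so randomisation protects neither. The both group belongs to neither side of a two-way contrast.

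**2. The plan's own sample size.** Inputs from the Sample size section: proportion 0.80, half-width 0.10, two-sided 95% interval. By the Wald formula, n = 1.96² × 0.80 × 0.20 / 0.10² = 61.46, rounded up to 62. The stated figure is reproduced. It rests on feasibility alone and does not depend on this point.

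**3. Precision of the within-arm contrast.** With 1:1 allocation, 62 / 2 = 31 per arm. Assume that 80% are evaluable: 31 × 0.80 = 24.8, about 25. The 80% is the article's feasibility criterion, borrowed here as an assumption and not a forecast. The splits are also assumptions, with the both group merged into one side. In SD units, half-width = 1.96 × √(1/a + 1/b):

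- 13 and 12: 1.96 × √(1/13 + 1/12) = 0.78 SD
- 18 and 7: 1.96 × √(1/18 + 1/7) = 0.87 SD

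With all 31 evaluable and split 16/15, it is 1.96 × √(1/16 + 1/15) = 0.70 SD.

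**4. Precision of a preference-by-arm interaction**, if preference were recorded in both arms, with the same splits in each arm. Half-width = 1.96 × √(2/a + 2/b):

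- 13 and 12: 1.96 × √(2/13 + 2/12) = 1.11 SD
- 18 and 7: 1.96 × √(2/18 + 2/7) = 1.23 SD

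**5. How large selection alone could be (illustration).** A simulation assumed no true difference between settings and one prognostic factor that drives the choice. With a factor–outcome correlation of 0.3 to 0.7 and an odds ratio for choosing one setting of 1.5 to 3 per SD of the factor, the apparent difference was 0.12 to 0.62 SD. None of these inputs is in the article, and the sign could go either way.

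**The case against.** The strongest reply is that the analysis is labelled exploratory, in a pilot whose primary objective is feasibility, and that no primary outcome or comparison of the randomised arms depends on it. That stands, and it limits the weight of the point. It does not remove it: an exploratory label excuses low power and multiplicity, but not a contrast described as something the design cannot identify.

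A second reply is that estimates are still possible. Each setting can be compared with all controls, or within the arm, and baseline frailty and SPPB are measured before setting is chosen, so adjustment is available. This also stands. A reader might infer that nothing at all can be estimated by setting, and that goes too far. What is unavailable is a randomised effect by setting. An adjusted estimate would rest on strong assumptions about who chooses what, and the article states none. The choice of covariates, and the handling of the both group within a model, may properly be left to an analysis plan that is not shown. Neither would supply the missing control values.

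A third reply is that small subgroups are imprecise in any pilot, including hip versus knee. That is true. The half-widths show how little the contrast could tell; they do not measure the defect, which is selection.

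Two stronger readings are tempting. One is that fitter or more mobile people will choose the center, so the center will look better. The documents do not say so. They name time and transportation as examples of barriers, and they describe the center program as designed for people with chronic bone and joint problems, with hydrotherapy and a physiotherapist available for consultation. Selection could run either way. The other is that this result will decide the delivery mode of the definitive trial. The article says that the pilot will inform that trial's design and lists effect sizes among the lessons, but it does not tie delivery mode to this analysis.

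**Conclusion.** The point holds in a limited form. As written, the plan presents as a subgroup effect a comparison on a variable that participants choose after learning their arm and that does not exist for controls. The result can only be a non-randomised contrast, confounded to an unknown extent and in an unknown direction. This conclusion follows from the article's own sequence of events and needs no numerical assumption.

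The size does rest on assumptions. With about 25 evaluable per arm and splits of 13/12 to 18/7, the within-arm half-width is about 0.78 to 0.87 SD.

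The consequence is confined to this exploratory analysis. The feasibility outcomes, the sample size of 62, the comparison of the randomised arms and the hip-versus-knee subgroup are unaffected.

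**What to change.** In the Data analysis section, remove the claim of a differential effect for exercise setting. State instead that setting used will be reported as a descriptive, non-randomised comparison within the intervention arm (uptake, adherence and outcomes), with participants who use both settings shown separately. Keep hip versus knee as the exploratory subgroup analysis. The cost is one sentence, with no new data.

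Optionally, for participants not yet enrolled, ask everyone in both arms for their preferred setting at the baseline visit, while they are still blind to allocation, and use the answer as an exploratory subgroup variable. Three limits should be stated with it:

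- It asks whether the effect varies with preference, not with the setting used.
- It would be very imprecise: about 1.11 to 1.23 SD on the assumptions above, before a third level is added.
- Recruitment was already under way and due to end around April 2018, so those enrolled earlier would have descriptive results only.

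This option costs a new baseline item in a running trial, which is more than a change of wording. The one-sentence relabelling is enough to resolve the point.
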